### Randomization and Blinding

Patients who have agreed to the trial will be screened on the day of screening (visit 0) whether they meet the inclusion/exclusion criteria. The enrolled participants will be randomly allocated to two parallel groups with a 1:1 ratio at the date of visit 1; either the Jaungo group or the moisturizer group. The random number will be generated by an independent statistician using a 2 × 2 randomized permuted block design. Each piece of paper with the allocation group information according to the random number will be sequentially inserted into an opaque envelope and sealed. After the screening, the enrolled participants will open the envelopes in order and will thus be assigned to either the Jaungo group or the moisturizer group.

Throughout the study process, the clinical research coordinator is responsible for recruiting participants, screening, and assigning random assignments. This trial is a single-blinded study because each intervention can be distinguished differently from the participants. The statisticians and envelope processors, group allocators, management pharmacists, and outcome assessors for the clinical trial are all independent. Additionally, the principal investigator and sub-investigator will be blinded to the assigned group.

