#### Exclusion Criteria

1) Cancer invasion to skin (T4 in eighth American Joint Committee on Cancer (AJCC) (Amin et al., 2017) TNM staging); 2) unhealed scar on the breast; 3) metastatic stage; 4) subjects who have a history of RT in the thoracic area for any reason; 5) soft tissue disease; 6) uncontrolled diabetes mellitus with an HbA1c value of 6.5% or greater; 7) subjects who are now or planned to be pregnant or breastfeeding during the study schedule; 8) subjects who are allergic to the medication; 9) Low compliance with any reason, including communication failure; and 10) abuse of alcohol or medication.

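### The coordinator who recruits and screens also assigns, although allocators are called independent; with one small permuted block, up to a third or a half of allocations could be deduced

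*Protocol article*

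**What the plan says.** All of this is in the protocol article, under Randomization and Blinding unless another section is named.

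- **Who assigns.** The article states that "the clinical research coordinator is responsible for recruiting participants, screening, and assigning random assignments". Shortly afterwards: "The statisticians and envelope processors, group allocators, management pharmacists, and outcome assessors for the clinical trial are all independent". It also says that "the enrolled participants will open the envelopes in order". No sentence says who holds the envelopes.
- **The list.** "The random number will be generated by an independent statistician using a 2 × 2 randomized permuted block design". Patients are "randomly allocated to two parallel groups with a 1:1 ratio at the date of visit 1". No other block size and no variation in size is mentioned.
- **The concealment device.** Each slip "will be sequentially inserted into an opaque envelope and sealed".
- **Masking.** The trial is single-blind because participants can tell the products apart. The principal investigator and sub-investigator are blinded, and under Outcome Measurement so are the assessing radiation oncologists. The coordinator is not among the roles said to be blinded.
- **Setting.** Study Design gives one centre. Sample Size gives 25 patients per arm. The Abstract says the trial is recruiting.
- **Room for judgement at entry.** Exclusion Criteria include "9) Low compliance with any reason, including communication failure".

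**The concern.** Concealment needs the person who decides on entry to be unable to foresee the next arm. Sealed opaque envelopes stop anyone reading the next slip. They do not stop someone who has seen the earlier slips in a permuted block from working out what is left. The shorter the block, the more often that is possible.

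As described, one role approaches patients, judges eligibility and takes part in assignment. In a single centre that role can see the whole run of past assignments. An exclusion that rests on judgement, such as expected poor compliance, leaves room for an expectation about the next arm to influence who enters, even unintentionally. The Discussion lists risk factors for dermatitis such as body mass index, breast volume and smoking. Several are apparent to a recruiter, and none is named under Demographic Characteristics.

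What is at stake is selection bias in the primary comparison of grade 2 or higher dermatitis. Blinded assessors protect against biased grading, not against arms that differ at entry. With 25 per arm, one patient moves an arm's incidence by 1/25 = 4 percentage points.

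**Working it through.** **The plan's own figure.** The article gives no figure for predictability. It does give the number of patients, which reproduces with the usual two-proportion formula for 0.467 against 0.09, two-sided 5%, 80% power: 21 per arm, then 21/0.85 = 24.7, so 25 per arm and 50 in total. This point does not change it.

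**The role statements side by side.** The coordinator recruits, screens and assigns. Participants open the envelopes. Group allocators are independent. The first and third conflict if independent means separate from enrolment, and the second does not settle who controls the envelopes.

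**Predictability.** Inputs: two arms, 1:1, and a block length of 4 (two places per arm) or 2, the two natural readings of 2 × 2. Assumption: the observer knows the length, the length is constant, and every past assignment has been seen.

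*Block of 2.* The second place is always forced.
- Certain: 1/2, or 25 of 50.
- Best guess correct: (0.5 + 1)/2 = 0.75.

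*Block of 4.* There are six equally likely sequences. AABB and BBAA force places 3 and 4. The other four force place 4 only.
- Certain per block: (2 × 2 + 4 × 1)/6 = 4/3, a share of (4/3)/4 = 1/3.
- Over 50 patients: 12 complete blocks give 12 × 4/3 = 16 certain. The first two places of a thirteenth block add none, so 16/50 = 32%.
- Best guess (the arm with more places left): 1/2, 2/3, 2/3 and 1 at the four places, so (0.500 + 0.667 + 0.667 + 1)/4 = 0.708 per complete block, and about 0.70 over 50 patients.

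*Varying lengths, order unknown to the observer* (simulation over 50 patients, sizes equally likely):

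| Block lengths | Allocations certain | Best guess correct |
|---|---|---|
| 2, constant | 50% | 75% |
| 4, constant | 32% | 70% |
| 2 and 4 mixed | 11% | 72% |
| 2, 4 and 6 mixed | 4% | 70% |

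The best-guess rate for the 2/4/6 mix can be checked by hand from the rates for complete blocks, the rate for length 6 being 0.683: (2 × 0.750 + 4 × 0.708 + 6 × 0.683)/12 = 0.70. It hardly moves because every block ends balanced, so the arm that is behind is the better guess whatever the block sizes are. Someone who does not see past assignments has only the 50% chance rate.

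**The case against.** **The roles may be compatible.** Assigning may only mean running the visit at which participants open envelopes that others prepared, and independent may mean that the listed roles are separate from each other. That reading is possible. It still leaves the recruiter present at each assignment, and the text does not choose between the readings.

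**The deduction needs conditions that are not stated.** The coordinator must know the block length, the length must be constant, and past assignments must be tracked. The article says none of this outright, and the list comes from an independent statistician. This stands: the one third and one half are ceilings under those conditions.

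**Screening comes first.** Eligibility is judged at visit 0 and the envelope is opened at visit 1. To exploit a forecast, the coordinator would have to anticipate who else is randomized in between. This weakens the mechanism. How far is unknown, because the accrual rate is not given.

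**An article condenses.** Whether block size is withheld from site staff may be settled in the full protocol, so its absence here is no finding. What the article does state is the assignment of roles, and that is what creates the exposure.

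**Stronger readings the article does not support.** A reader might infer that the trial is unmasked; it is single-blind, with blinded investigators and assessors. A reader might infer that a third to a half of upcoming arms are in fact known beforehand, or that the coordinator keeps and opens the envelopes. Neither is stated, and nothing shows that allocation was manipulated.

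**Conclusion.** The point holds as an avoidable weakness in the stated procedure, not as evidence that concealment failed. The firm part is textual: the same paragraph gives recruiting, screening and assigning to one role and calls the allocators independent.

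The size depends on assumptions. With a constant block length known to the coordinator and past assignments tracked, about one third (blocks of 4) or one half (blocks of 2) of allocations could be deduced with certainty. If the 2 × 2 wording covered a random mix of 2 and 4, it would be about 11%. If the coordinator does not follow the sequence, the exposure disappears. No bias in the primary incidence can be estimated from the article. If selection did occur, adjustment could not be relied on to repair it. The change is worth making because recruitment is under way and the remedy is cheap.

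**What to change.** 1. **Reconcile the roles (main remedy).** Rewrite Randomization and Blinding so that the independent group allocator or management pharmacist it already names holds the envelopes and releases each one. The coordinator recruits and screens but does not assign. Whoever judges eligibility should not keep or consult a record of past assignments. The existing order, screening before opening, should stay.
2. **Vary the blocks.** Have the independent statistician generate the remaining list with randomly varying block sizes, for example 2, 4 and 6, not disclosed to site staff. This takes certain allocations from about 32% (constant blocks of 4) to about 4%. It leaves best-guess accuracy near 70% for anyone who tracks the sequence, so it supports step 1 and does not replace it.

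**Cost.** The roles already exist, so no new staff are needed. It does require an amendment to the procedure while patients are being recruited, and the number already randomized is not given, so the benefit applies only to those still to come. The arms may end a few patients apart. The sample size is unchanged. Because participants can tell the products apart, the coordinator may still hear of some assignments, so the separation reduces the risk without removing it.

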### Treatment Protocol

#### Radiation Therapy

All subjects will receive RT, regardless of the type of intervention. Patients will undergo 3-dimensional conformal RT (3D-CRT) or intensity-modulated RT (IMRT) for a maximum period of 7 weeks after breast cancer surgery according to the National and International Guidelines. The tumor bed will be treated with a biological equivalent dose (BED_10_) of 60 Gy or more, with a schedule of five fractions weekly for 5–7 weeks. In some cases, regional lymph nodal irradiation will be delivered with risk factors for regional recurrence, such as invasion of lymphovascular or axillary lymph nodes.

#### Intervention

The research will be conducted for a total of 7–9 weeks with nine individual assessments, consisting of topically administrating the Jaungo (Hanpoong Pharm & Foods Corporation, Seoul, South Korea) or the moisturizer (X-derm^®^, Pharmbio Korea Corporation, Seoul, South Korea) for the period of RT, 5–7 weeks, through eight visits after screening and a follow-up 2 weeks after the end of the application. The participants assigned to the Jaungo group will apply Jaungo on the entire irradiated skin region three times a day from the first day of RT, with a 1 cm distance from the skin marking line. The moisturizer group will apply the moisturizer in the same process.

#### Contraindications of Intervention

1) The intervention medications should not be used in patients with a history of hypersensitivity to the drugs, severe or extensive trauma, high fever in the suppuration area, and severe eczema or maceration in the radiated lesion; 2) in the case of skin irritation, local rash, or itching during the use of intervention medications, the application should be stopped; 3) the intervention medications should only be used as topical agents; 4) the intervention medications should be stored in a cool place away from direct sunlight.

### Outcome Measurement

The participants will be assessed at every visit during RT and 2 weeks after the end of RT. The assessment will be conducted by radiation oncologists who do not know which group the participant belongs to, and will be single-blinded. The date of the occurrence and severity of RID will be evaluated at every visit from the start to end of RT and 2 weeks after, based on the RTOG grade. An incidence rate of Gr ≥ 2 RID will be recorded as the primary outcome of this study. At the start and end of RT and 2 weeks later, the quality of life (QOL), skin reaction symptoms, and maximum pain related to RID will be measured based on the Catterall skin scoring profile (CSSP) (Catterall et al., 1971), the Korean version of Skindex-29 (Ahn et al., 2004), and numeric rating scale (NRS) (Haefeli and Elfering, 2006). The maximum grade of RID, time to onset of RID, the value of CSSP, the Korean version of Skindex-29, and NRS, and the types and frequencies of adverse events will be compared as secondary outcomes between the two groups.

#### Demographic Characteristics

Sex, age, ECOG performance status, and history of the disease are included in the demographic characteristics.

#### RTOG Grade

The RTOG toxicity scale was developed by the Radiation Therapy Oncology Group in the United States, which measures the grade of skin tissue damage caused by RT (Cox et al., 1995) and is classified into 0–4 grades according to the symptoms of dermatitis: Gr 0, no change over baseline; Gr 1, follicular, faint or dull erythema, epilation, dry desquamation, decreased sweating; Gr 2, tender or bright erythema, patchy moist desquamation, moderate edema; Gr 3, confluent, moist desquamation other than skin folds, pitting edema; Gr 4, ulceration hemorrhage, necrosis.

#### Catterall Skin Scoring Profile

The CSSP was developed by Fowler to allow the evaluation of skin reaction in mice, and was later modified by Catterall in 1965 to apply a numeric scale-type assessment tool (Catterall et al., 1971). It is classified as 1–10 points, depending on the symptoms and severity of dermatitis: 1, no visible reaction; 2, light erythema; 3, moderate erythema; 4, severe erythema; 5, dry desquamation <50% of irradiated are; 6, dry desquamation >50% of irradiated area; 7, blistering present; 8, moist desquamation <50% of the irradiated area; 9, moist desquamation >50% of the irradiated area; 10, ulceration present.

#### Skindex-29

Skindex-29 is a revision of the existing 61 questions of Skindex to 29 questions for patients with skin diseases. Skindex-29 is a QOL assessment tool designed to evaluate the QOL of a patient on three scales of symptoms, function, and emotion, while maintaining excellent reproducibility, reliability, recruitment validity, and content validity of Skindex. In this study, we will use the Korean version of Skindex-29 published by Ahn et al. (2004), which is a 5-level Likert scale from 1 (never) to 5 (always) and has been validated.

#### Numeric Rating Scale

NRS is a pain evaluation tool that uses the visual pain score (Haefeli and Elfering, 2006). NRS 0 is defined as the state without discomfort, and NRS 10 is the maximum degree of discomfort that the patient can think of.

#### Adverse Events

Clinical adverse events will be evaluated based on the Common Terminology Criteria for Adverse Events (CTCAE), version 5.0, developed by the NCI (Freites-Martinez et al., 2021). The research manager will check for adverse events during the period of intervention medication use at each visit. Information on adverse events is provided to participants reporting to the research manager, and the manager checks the occurrence of adverse events through a questionnaire at each visit. The notified events will be recorded in the “Adverse Reaction Record Table”. Adverse events will also be reported in detail on the date of onset and disappearance, the severity and outcome of events, the treatment taken in relation to the events and the causal relationship with the intervention, and the name of the suspected drug other than the intervention.

### Data Collection and Management

The participants will visit the outpatient clinic every week with a 3-day visit window during RT and 2 weeks after the end of RT. Figure 2 shows the study procedure and outcome measurements.

**FIGURE 2 F2:**
[figure not shown]
Study procedures and outcome measurements.

One or two assistants will collect and record the entire data in electronic case report forms. Personal information will be stored in an independent storeroom to protect confidentiality. The contract research organization (CRO) will monitor the data, protocol, and safety of this study and check the source documents every month. Access to the online database will be restricted to radiology oncologist researchers in this study team, as well as non-related outside people.

### Statistical Analysis

The collected data will be statistically assessed using SPSS Version 25.0 (Chicago, IL), based on the intention-to-treat (ITT) set, except for the following subjects: 1) subjects who violate the inclusion/exclusion criteria; 2) subjects who have never used the intervention medication; and 3) subjects who have not provided any data after screening. The demographic characteristics of all participants will be reported as the mean and 95% confidence interval (95% CI) for continuous variables or frequencies and percentages for categorical variables. The incidence rate of RTOG Gr ≥ 2 RID, the primary outcome of this study, will be evaluated the difference between two groups using the Chi-squared test. Among the secondary outcomes, the maximum grade of RID based on RTOG will be analyzed by Chi-squared test, the time to RID occurrence by Kaplan-Meier analysis, and the CSSP, Skindex-29, and the maximum NRS for RID-related pain by independent sample t-test or Mann-Whitney U test, depending on the normal distribution, to compare the differences between the two groups. Adverse events will be presented as descriptive statistics by dividing according to the severity of each intervention and adverse symptoms. The types and frequencies of adverse events determined to be causative of the intervention will be separately analyzed and reported. Differences will be considered statistically significant when *p* < 0.05. Adverse reactions will be presented as descriptive statistics, divided according to the severity of each group and each adverse event. The symptoms and frequencies of adverse reactions related to the intervention medication will be analyzed separately.

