#### Drop-Out Criteria

Any patient who meets one of the following conditions will be dropped out from the trial. 1) The subjects or their families withdraw consent to participate in the trial; 2) a violation of the inclusion/exclusion criteria is found during the trial; 3) a significant adverse event appears in the subject and/or it is difficult to continue the trial due to an adverse reaction; 4) any violation of the study protocol; 5) the compliance level of the intervention (Jaungo or moisturizer) is less than 70%; 6) subjects who take medications, etc. that may affect the results of this study without confirmation from the attending physician; 7) any cases that the attending physician judge as inappropriate to the trial; 8) subjects who pregnant during the trial period; 9) subjects who fail to follow up during the trial period; 10) subjects who died during the trial period.

The methods used to contact the subject must be recorded in the supporting documents in the case of subjects who fail to follow up to prove that reasonable efforts were made to contact them. The patients who dropped-out due to significant adverse events could be provided with appropriate treatment for side effects. In these cases, the attending physician shall continuously evaluate the subjects until the adverse reactions are resolved or determined to be permanent.

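### The one population rule in Statistical Analysis, read as written, takes a treated patient later found ineligible out of the adverse-event summaries by group

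*Protocol article*

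**What the plan says.** All references are to the protocol article.

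- **Population.** Statistical Analysis opens with a general rule: "The collected data will be statistically assessed using SPSS Version 25.0 (Chicago, IL), based on the intention-to-treat (ITT) set". Three kinds of patient are then taken out of that set: "except for the following subjects: 1) subjects who violate the inclusion/exclusion criteria; 2) subjects who have never used the intervention medication", and third, those who supplied no data past screening.
- **Demographics.** The next sentence widens the scope for one item: "The demographic characteristics of all participants will be reported".
- **Adverse events.** The same section plans "Adverse events will be presented as descriptive statistics by dividing according to the severity of each intervention and adverse symptoms" and adds: "The types and frequencies of adverse events determined to be causative of the intervention will be separately analyzed and reported". Neither sentence names a population, and the article defines no safety or as-treated set.
- **Role of adverse events.** Outcome Measurement lists them among the secondary outcomes to be compared between the two groups.
- **Timing of eligibility findings.** Eligibility is checked before allocation: "Patients who have agreed to the trial will be screened on the day of screening (visit 0) whether they meet the inclusion/exclusion criteria". The Drop-Out Criteria nevertheless provide, as item 2, for the case that "a violation of the inclusion/exclusion criteria is found during the trial".
- **Collection.** The Adverse Events section has events checked at each visit while the product is in use and recorded with dates, severity, outcome, treatment and causality.

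**The concern.** Whether a patient can react to a topical product depends on having applied it, not on having met the entry criteria. A safety summary should therefore count everyone exposed. Here the only population rule removes eligibility violators whether or not they were exposed; never-users are dealt with separately, in the second exclusion. If the rule is followed as printed, a treated patient found ineligible in week 3, say, leaves both the numerator and the denominator of the adverse-event table for that arm.

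At stake is the completeness of a descriptive secondary outcome. With about 25 patients per arm, one patient can be the only instance of an event type, and removing that patient empties the row for that arm. No efficacy test depends on this.

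**Working it through.** **Step 1: does the rule reach adverse events?** The subject of the opening sentence is the collected data, without restriction, and adverse events are collected data. The section departs from the rule explicitly once, for demographics. It makes no such departure for adverse events. On the text alone the rule applies.

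**Step 2: which exclusion does harm?**

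- Exclusion 1 (eligibility violation) has no condition on exposure or timing, so it can remove an exposed patient with recorded events.
- Exclusion 2 (never used the product) removes only unexposed patients. It is harmless for safety.
- Exclusion 3 (no data past screening) removes patients with no recorded event to count.

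Only exclusion 1 matters here.

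**Step 3: can the case arise?** Yes. Drop-out item 2 foresees it. Screening at visit 0 should make it uncommon. The article gives no rate, so the results below are conditional on the number k of treated patients removed from an arm.

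**Step 4: arm size.** The Sample Size section states 25 per group. The pooled two-proportion formula reproduces this with rates 0.467 and 0.09, two-sided 5% and 80% power. The mean rate is 0.2785 and the difference 0.377:

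n = [1.960 × √(2 × 0.2785 × 0.7215) + 0.8416 × √(0.467 × 0.533 + 0.09 × 0.91)]² / 0.377² ≈ 20.97, rounded up to 21 per arm.

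21 / 0.85 = 24.7, rounded up to 25 per arm, 50 in total.

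The point does not depend on how 25 was obtained. It serves only as the denominator, assuming all 25 start treatment.

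**Step 5: one treated patient removed (k = 1).** Exact (Clopper-Pearson) 95% intervals:

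| Case | All treated | After removal |
|---|---|---|
| Removed patient had the only event | 1/25 = 4.0% (0.1% to 20.4%) | 0/24 = 0% (0% to 14.2%) |
| Removed patient had one of five | 5/25 = 20.0% (6.8% to 40.7%) | 4/24 = 16.7% (4.7% to 37.4%) |
| Removed patient had no event, five others did | 5/25 = 20.0% (6.8% to 40.7%) | 5/24 = 20.8% (7.1% to 42.2%) |

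The rate can move either way, and the intervals overlap widely.

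**Step 6: chance of losing a singleton event type.** Assume that removal is random with respect to events and that the event type occurs in exactly one of 25 patients. Then

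P(lost) = 1 − C(24, k) / C(25, k) = k / 25.

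This is 0 for k = 0, 4% for k = 1 and 8% for k = 2.

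**The case against.** The strongest reply is that this is only a missing safety-set definition, which a condensed article may leave to the full protocol or the analysis plan. The exclusions may have been meant for the efficacy comparisons alone. The demographics sentence shows that the opening rule is not applied to everything in the section, and the adverse-event sentences speak of descriptive presentation rather than statistical assessment. Elsewhere the article points towards keeping events: they are checked at every visit and recorded in detail, patients dropped for significant events are followed until resolution or permanence, and the contract research organization monitors safety.

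Part of this stands. An efficacy-only intent is possible, and the absence of a safety set would not by itself be a finding. But the article does more than stay silent: it states a rule for all collected data, and nothing exempts adverse events from it. The provisions on recording, follow-up and monitoring govern what is collected, not whose events enter the group summaries. An analysis plan that followed the printed rule would carry the exclusion forward.

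Two stronger readings are tempting, and the documents support neither.

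- A reader might infer that the plan means to discard safety data, or that the events go unrecorded. The text does not say so, and the case record is kept; what is at risk is the count by group.
- A reader might infer that patients who react to the product are themselves excluded, since allergy to the medication is an exclusion criterion. That criterion most naturally applies at entry. A reaction on treatment falls under a separate drop-out reason, "a significant adverse event appears in the subject and/or it is difficult to continue the trial due to an adverse reaction", and that reason is not among the three analysis exclusions.

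**Conclusion.** The point holds as a minor one. Followed literally, exclusion 1 removes a treated patient later found ineligible from the adverse-event summaries of the group. This rests on reading the opening sentence of Statistical Analysis at face value; the authors may have intended a narrower scope but did not write it.

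The size is small and conditional. If no violation is found after treatment starts, nothing changes. If one patient is removed from an arm of 25, a singleton event type disappears from the table with probability 4% under random removal, and rates otherwise move by about one to four percentage points in the cases shown. The number of late findings is unknown and probably low. The sample size, power and efficacy conclusions are unaffected.

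**What to change.** Add one sentence to Statistical Analysis: exclusion 1 (eligibility violation) does not apply to adverse events, which are summarised by group for every patient who applied a product at least once, regardless of later eligibility findings or drop-out. Exclusion 2 can stay, since limiting the summary to patients who applied a product already implies it.

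The cost is that sentence. Events are already checked at each visit, so no new data collection is planned. Reported event rates may shift slightly up or down compared with the printed rule.

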### Sample Size

In this pilot study, the sample size was estimated according to the grade (Gr) of the Radiation Therapy Oncology Group (RTOG) (Cox et al., 1995) and National Cancer Institute (NCI) (Trotti et al., 2000) for the RID reported in the relevant literature. Kong et al. (Kong et al., 2016) investigated the incidence rate of RTOG Gr ≥ 2 in breast cancer patients with RID using Jaungo, which is the primary outcome in this study, at 46.7%. For non-steroidal moisturizer, there was no primary report using RTOG grade, but the incidence rate of NCI Gr ≥ 2 of RID in breast cancer patients was 9.0% (Leonardi et al., 2008). Clinically, the RTOG and NCI are common assessment grading tools, and each value of the incidence rate is compatible. Therefore, we estimated the incidence rates of the Jaungo and the moisturizer groups to be 0.467 and 0.09, respectively. The formula for calculating the sample size is as follows:$$n_{c}=\;\frac{\left(1+\lambda \right)\sigma^{2}{\left(Z_{\alpha /2}+Z_{\beta }\right)}^{2}}{\lambda d^{2}}$$

At the 5% significance level, considering an estimated withdrawal rate of 15%, a total of 50 participants, 25 in each group will be required to achieve 80% power.

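### Maximum RTOG grade, an ordered 0–4 secondary outcome, is tested with a plain chi-squared test that ignores grade order and has sparse cells at 21–25 patients per arm

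*Protocol article*

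**What the plan says.** The RTOG Grade section describes a scale that "measures the grade of skin tissue damage caused by RT" and "is classified into 0–4 grades according to the symptoms of dermatitis", running from no change to ulceration, haemorrhage and necrosis. It is therefore ordered.

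The Outcome Measurement section makes the maximum grade one of several secondary outcomes ("The maximum grade of RID, time to onset of RID, the value of CSSP" and others). It is separate from the binary primary outcome, grade 2 or higher.

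The Statistical Analysis section then fixes the test: "the maximum grade of RID based on RTOG will be analyzed by Chi-squared test". This is the test also named for the binary primary outcome, and no trend version is mentioned. The same sentence allows a t-test or a Mann-Whitney U test for CSSP, Skindex-29 and NRS. CSSP is itself an ordered skin-reaction score, from 1 to 10.

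On size, the Sample Size section says that "a total of 50 participants, 25 in each group will be required to achieve 80% power" and that "we estimated the incidence rates of the Jaungo and the moisturizer groups to be 0.467 and 0.09, respectively".

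**The concern.** Read plainly, the test is Pearson's chi-squared on a table of two arms by up to five grades. It has three problems here.

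- **Order is discarded.** Swapping the labels of grades 1 and 3 would leave the statistic unchanged. The test spreads its sensitivity over up to 4 degrees of freedom instead of concentrating it on the question of interest, which is whether one arm has milder skin reactions.
- **No direction or effect size.** A significant result says only that the two grade distributions differ. It could arise because one arm has more patients at both ends of the scale.
- **Sparse cells.** With about 42 to 50 patients over four or five grades, several expected counts are small and the chi-squared approximation is poor.

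At stake is the efficiency and readability of one secondary severity comparison. The plan also treats two ordered skin scales differently, RTOG as unordered categories and CSSP with a rank test available, and gives no reason.

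**Working it through.** **1. The plan's sample size.** The usual two-proportion formula with 0.467 versus 0.09, two-sided 5% and 80% power, without continuity correction, gives 21 per arm (power 0.80). Allowing for 15% withdrawal, 21 / 0.85 = 24.7, so 25 per arm and 50 in total. The stated figure reproduces. The table will therefore hold about 21 to 25 patients per arm.

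**2. Assumed grade shares.** The article does not give a full grade distribution.
- Jaungo: grade 2 or higher 46.7% (Sample Size) and grade 3 20.0% (Discussion, earlier Jaungo study), so grade 2 alone is 46.7 − 20.0 = 26.7%.
- Moisturizer: grade 2 or higher 9%. A split of 7% grade 2 and 2% grade 3 is an assumption.
- Grade 0: assumed and varied. The Introduction and Discussion put any RID at about 90–95%, which suggests 5–10%.
- Grade 4: taken as empty in the runs shown here.

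**3. Expected counts.** With equal arms, the expected count per arm in a grade is n × (share in arm 1 + share in arm 2) / 2. With grade 0 at 10% in both arms and n = 21:
- grade 0: 21 × (0.10 + 0.10) / 2 = 2.1
- grade 1: 21 × (0.433 + 0.81) / 2 = 13.1
- grade 2: 21 × (0.267 + 0.07) / 2 = 3.5
- grade 3: 21 × (0.20 + 0.02) / 2 = 2.3

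Three of four non-empty grades are below 5. At n = 25 the counts are 2.5, 15.5, 4.2 and 2.8, again three of four. Across the scenarios, the average share of expected counts below 5 was about 30–70%, and 97–100% of simulated tables had more than 20% of expected counts below 5.

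**4. Tests compared.** At least 10,000 simulated trials per scenario, with empty grades dropped:
- Pearson: sum of (observed − expected)² / expected, on k − 1 degrees of freedom for k non-empty grades.
- Mann-Whitney: rank sum with mid-ranks and tie-corrected variance, two-sided 5%.

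**5. Behaviour under the null.** With the moisturizer shares in both arms, Pearson rejected 2.4–2.6% and Mann-Whitney 4.5–5.0%. With the Jaungo shares in both arms, Pearson rejected 4.4–4.9% and Mann-Whitney 5.2–5.3%. Pearson stays at or below the nominal level and is clearly conservative when high grades are rare.

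**6. Power for a shift across the whole scale** (21 / 25 per arm). The design-rate odds ratio is (0.91/0.09) / (0.533/0.467) = 8.9.

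| Scenario | Chi-squared | Mann-Whitney |
|---|---|---|
| Proportional odds, OR 3 | 28% / 36% | 45% / 52% |
| Proportional odds, OR 4 | 44% / 53% | 64% / 72% |
| Earlier-study contrast (46.7% vs 78.6% grade ≥ 2; 20% vs 50% grade 3; grade 0 assumed 10% vs 5%) | 50% / 59% | 64% / 73% |
| Planning rates as a proportional-odds shift, OR 8.9 | 85% / 91% | 95% / 97% |

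The loss is about 6 to 20 points. The linear-by-linear test stays within about 2 points of Mann-Whitney in these rows.

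**7. Power under the planning rates, varying only the assumed grade 0 share** (21 / 25 per arm).

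| Grade 0, Jaungo vs moisturizer | Chi-squared | Mann-Whitney |
|---|---|---|
| 10% vs 10% | 67% / 77% | 64% / 71% |
| 5% vs 5% | 67% / 77% | 73% / 80% |
| 10% vs 15% | 65% / 75% | 69% / 76% |
| 10% vs 20% | 64% / 74% | 75% / 81% |
| 5% vs 10% | 64% / 75% | 78% / 85% |

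The difference runs from about 5 points in favour of chi-squared (3 at 21 per arm, 6 at 25) to about 13 points in favour of Mann-Whitney.

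**The case against.** **The power gain is not guaranteed.** This stands. If the arms share the same grade 0 rate and differ only above grade 1, chi-squared can be as good or slightly better, as the first row of step 7 shows. The shifts in step 6 also move grade 0 a good deal: OR 3 takes a 10% share to (0.10/0.90 × 3) / (1 + 0.10/0.90 × 3) = 25%, more than the article's 90–95% RID figures suggest.

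**The 14-point loss in the earlier-study contrast is not this trial's loss.** A reader might carry that figure over. The Discussion's comparator there was supportive skincare with soap washing and no moisturizer. This trial's comparator is a moisturizer, with its own planning rate of 9%.

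**Sparse cells do not mean false positives.** A reader might infer an inflated error rate. The simulations show the reverse: Pearson rejects at or below the nominal level. It remains a valid test that the two grade distributions are equal.

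**This is one of several secondary outcomes in a pilot.** This stands too. The article nowhere singles out maximum grade as its leading severity measure, and CSSP also measures skin severity.

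**An article may leave details to the full plan.** An exact fallback and the grade table by arm may be specified there, so their absence is not held against the plan. The named test is different, because the article states it.

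**Conclusion.** The point holds as a minor matter of efficiency and interpretation. An ordered outcome is given a test that ignores its order and yields no direction, on a table that will almost certainly be sparse and on which the test tends to be conservative. Against a consistent shift in grade the cost is about 6–20 points of power. Under the trial's own planning rates the rank test's advantage lies between about −5 and +13 points.

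These sizes rest on assumed grade 0 shares and an assumed 7%/2% split of moisturizer grades 2 and 3, so no single figure should be quoted as the loss. The loss of ordering and the sparse cells do not depend on which of these scenarios is true. The documents do not support a claim that chi-squared is always weaker, that it inflates false positives, or that the trial's main conclusion is at risk. The binary primary outcome and the 50-patient sample size are untouched.

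**What to change.** Replace the clause on maximum RTOG grade with a test that uses the ordering: the tie-corrected Mann-Whitney test or the linear-by-linear association test, with exact p-values. Report an ordinal effect measure with its 95% CI, either a proportional-odds ratio or the probability that a patient in one arm has a lower grade than a patient in the other. Showing the grade counts by arm beside it would make the direction plain.

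The cost is one sentence, with no extra data or patients. Mann-Whitney is already in the plan for CSSP, so the two skin scales would then be treated alike. The downside is slightly lower power if the arms differ only above grade 1. The article describes recruitment as ongoing, so the change should be recorded before any outcome data are compared by arm.
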